# A cluster-randomised controlled trial to promote physical activity in adolescents: the Raising Awareness of Physical Activity (RAW-PA) Study

**DOI:** 10.1186/s12889-016-3945-5

**Published:** 2017-01-04

**Keywords:** Online, Leisure time, Sedentary behaviour, Wearable technology, Pedometer

## Abstract

**Background:**

Recent technological advances provide an alternative yet underutilised opportunity for promoting physical activity in youth. The primary aim of the Raising Awareness of Physical Activity (RAW-PA) Study is to examine the short- and longer-term impact of a wearable activity monitor combined with digital behaviour change resources on adolescents’ daily physical activity levels.

**Methods/Design:**

RAW-PA is a 12 week, multicomponent physical activity intervention that utilises a popular activity tracker (Fitbit® Flex) and supporting digital materials that will be delivered online via social media. The resources target key behaviour change techniques. The intervention structure and components have been informed by participatory research principles. RAW-PA will be evaluated using a cluster randomised controlled trial design with schools as the unit of randomisation. Twelve schools located in Melbourne, Australia, will allocated to either the intervention or wait-list control group. The target sample size is 300 Year 8 adolescents (aged 13–14 years). Participants’ moderate- to vigorous-intensity physical activity will be the primary outcome. Survey measures will be completed. Process factors (e.g. feasibility, acceptability/appeal, fidelity) will also be collected.

**Discussion:**

To our knowledge, this study will provide some of the first evidence concerning the effect of wearable activity trackers and digital behaviour change resources on adolescents’ physical activity levels. This study will provide insights into the use of such technologies for physical activity promotion, which may have a significant impact on health education, promotion, practice and policy.

**Trial registration:**

Australian and New Zealand Clinical Trials Registry No: ACTRN12616000899448. Date of registration: July 7, 2016.

## Background

Regular physical activity benefits youth physical, social, mental and emotional health, including psychological well-being, bone health and fitness [1]. In contrast, low levels of physical activity are associated with the increased likelihood of cardiovascular disease risk factors including metabolic syndrome, higher waist circumference, and overweight/obesity [2]. However, only 13% of Australian 12–14 year olds [3] engage in 60 min of moderate- to vigorous-intensity physical activity (MVPA) every day - the current recommendation for health [4]. Low guideline compliance has also been observed in other developed countries [5–7]. Adolescence is an age where declines in physical activity levels are common [8]. This is of particular concern as this life-stage represents a time where health inequities start to emerge, and these may extend into adulthood [9]. For example, those living in socioeconomically disadvantaged areas are at a greater risk of declines in their activity levels [10] and are less likely to meet national activity guidelines [11]. Consequently, primary preventative measures targeting adolescents, particularly among those living in disadvantage, are warranted.

The majority of physical activity interventions in young people have targeted primary school children, with fewer initiatives designed specifically to increase activity levels in adolescents [12, 13]. There is also a lack of intervention studies that have specifically targeted the promotion of activity levels of adolescents living in disadvantaged neighbourhoods [14]. Of those conducted, a number targeted a single sex [15–18] and most have used multicomponent approaches delivered through school-based settings [15, 16, 19–21]. Such interventions can be resource-intensive, costly and are usually conducted in class, which can be difficult to implement due to an already crowded curriculum. All of these factors have a negative impact on the reach and sustainability of such approaches. In addition, existing approaches have often focused on sport [13, 20, 21], which may not be appealing to inactive adolescents who have little or no involvement in organised sport [22]. As such, there is a need for further research to examine non-curriculum based, lower resource intensive approaches for promoting physical activity levels in adolescents living in socioeconomically disadvantaged areas.

Recent technological advances provide an alternative, yet underutilised opportunity for promoting physical activity in youth. Wearable activity trackers (e.g. Fitbit®, Garmin®, etc.) are self-monitoring tools that have the capacity to track physical activity in real-time and provide individualised feedback against set goals and physical activity recommendations. They are accompanied by apps and/or web-based portals that incorporate a range of behaviour change techniques, including social support, prompts/cues, biofeedback, and focus on past successes [23, 24]. Notably, such technologies have considerable mass market appeal, are increasingly popular, and are being widely adopted across all age and socioeconomic groups [25]. For example, in the US, one in 10 adults own an activity tracker and ~60% continue to use it after 12 months [26]. In Australia, 20% of adults own a wearable activity tracker [25]. Whilst there are no data available concerning adolescent ownership or use of activity trackers, these technologies are likely to have substantial appeal to youth as they are often early adopters of new technologies [27]. Despite this, little research has examined whether these devices can be effectively utilised to increase physical activity among adolescents [28]. The majority of interventions using such devices have focused on adults, with mixed evidence concerning the efficacy of wearable devices for increasing overall activity levels [24, 29, 30].

Some research has suggested that wearable activity trackers can motivate individuals to make enduring changes to their daily activity [31]. However, several recent studies conducted with adults have questioned the value of such devices for promoting physical activity levels, suggesting that self-monitoring alone may not be sufficient to increase activity levels and that additional support may be required to help change behaviour [29, 32]. Online programs (e.g., web-based programs providing social support, tailored programs), social media platforms (e.g., Facebook groups), and digital resources such as videos, images, and infographics may help to overcome this limitation and educate and provide individuals with behaviour change techniques and skills. In addition, online programs have significant advantages in that they are able to reach a large target audience, are readily accessible, and use social connections and networks to engage and motivate participants [33]. Since recent data suggest that 96% of adolescents in this target age group have home internet access [34], and Facebook is the most popular and frequently used social media platform [35], integrating wearable activity trackers with digital behaviour change resources hosted online on social media platforms may be one intervention strategy that can positively influence physical activity levels in this target group.

This paper provides a rationale and description of the Raising Awareness of Physical Activity (RAW-PA) Study protocol; an innovative physical activity intervention that combines wearable activity trackers with online digital behaviour change resources for inactive adolescents attending schools in socioeconomically disadvantaged areas.

### Aims

The primary aim of RAW-PA is to examine the short- and longer-term impact of a wearable activity tracker combined with behaviour change resources on adolescents' daily MVPA. In order to understand patterns of change in activity levels (e.g., How do activity intensities change? When during the day do changes occur?), this study will evaluate the short- and longer-term impact on sitting time and MVPA across the whole day and during periods of the day (e.g., school hours). In addition, given the scarcity of evidence with this target population, this study will evaluate the impact of the intervention on potential mediators (e.g. self-efficacy, social support, etc.) to examine how the intervention effected change. Lastly, this study will examine process factors (feasibility, acceptability/appeal, fidelity).

## Methods

### Study design overview

RAW-PA will be evaluated using a cluster randomised controlled trial (cluster-RCT) design with secondary schools being the unit of randomisation. The intervention will target adolescents in Year 8 (second year of secondary school) in 12 co-educational, government funded schools in Melbourne, Australia. The intervention will run for 12 weeks, with assessments to be conducted at baseline, post-intervention and at 6-month follow-up (see Table 1 for the proposed study timeline). The design, conduct and reporting of this RCT will adhere to the Consolidated Standards of Reporting Trials (CONSORT) guidelines. Ethical approval was obtained from Deakin University Human Research Ethics Committee (2016–179) and the Victorian Department of Education and Training. The trial is registered with the Australian and New Zealand Clinical Trials Registry (ANZCTR): ACTRN12616000899448.

**Table 1 Tab1:**
[figure not shown]
Proposed timeline of RAW-PA Study

### Settings and participants

The Socio-Economic Index for Areas (SEIFA [36]) will be used to identify socioeconomically disadvantaged suburbs (SEIFA index of ≤5) in Victoria, Australia. SEIFA summarises the characteristics of people and households within an area and uses a number of criteria, including employment, education, housing stress and family type [36]. The My School website (www.myschool.edu.au) will then be used to identify schools located in socioeconomically disadvantaged suburbs that are located within ~60 km of Deakin University’s Burwood Campus. Eligible schools will be randomly selected and invited to participate in the study until 12 schools agree. Eligible study participants will be adolescent males and females who are in Year 8, are at least 13 years old (minimum age required to have a Fitbit® and a Facebook account) and attend one of the recruited schools. Eligibility criteria include: (1) having access to the Internet outside of school (via smartphone or home Internet); (2) having (or willing to create) a Facebook account; (3) not engaging in regular organised physical activity/sport outside of school (at least once per week throughout the year); (4) not meeting national physical activity guidelines of at least 60 min of MVPA every day; and (5) not a current or past owner of an activity tracker. Eligibility will be determined based on a checklist completed by parents and students. The first 25 eligible students from each school to return a completed informed written parental consent form (which includes student assent) will be recruited into the study.

### Sample size

Previous population-based studies were used to estimate the SD of mean daily minutes of MVPA (18.6 [37]) and the intraclass correlation coefficient for clustering within schools (ICC; 0.01 [38]). Based on an initial sample size of 300 adolescents (150 per study arm) participating from 12 schools (25 students per school), the z-statistic for 80% power is 0.84 and the z-statistic for α = 0.05 is 1.96. Based on 70% providing usable data at post-intervention, it was estimated that there would be 210 students (105 per arm) at post-intervention. With this sample size, the study is able to detect a difference in the mean daily MVPA between intervention and control students of 7.9 min at post-test.

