### Blinding and randomisation

In this cluster-RCT, recruitment and baseline data collection will be conducted prior to randomisation. Schools will be match-paired based on their size and SEIFA score and randomly allocated to either the intervention (6 schools) or wait-list control (6 schools) group by a computer-based random number generator. Randomisation will be conducted by an independent researcher not involved in the current study. Participants attending schools randomised to the intervention group will commence the program once baseline measures have been completed for all participants. Participants in the wait-list control group will be provided access to the intervention materials after the completion of the 6-month follow-up assessments.

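### The 7.9 min detectable difference makes no allowance for randomising only 12 schools: with school-level degrees of freedom, power at 7.9 min is about 71–73%, and 80% power needs about 8.6–8.8 min

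*Protocol article*

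**What the plan says.** The protocol article's 'Sample size' section takes an SD of 18.6 min for mean daily MVPA and a school ICC of 0.01 from earlier population-based studies. It plans for "300 adolescents (150 per study arm) participating from 12 schools (25 students per school") and then allows for loss: "Based on 70% providing usable data at post-intervention, it was estimated that there would be 210 students (105 per arm) at post-intervention". The multipliers are printed: "the z-statistic for 80% power is 0.84 and the z-statistic for α = 0.05 is 1.96". The conclusion is that "the study is able to detect a difference in the mean daily MVPA between intervention and control students of 7.9 min at post-test".

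Under 'Blinding and randomisation', schools are matched in pairs on size and SEIFA score and then "randomly allocated to either the intervention (6 schools) or wait-list control (6 schools) group". 'Data analysis' plans multilevel modelling of adolescents within schools, adjusted for potential confounders, with wear time and sex as examples. It names no reference distribution for the arm effect. The sample-size section counts no precision gain from matching or from covariates.

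**The concern.** The sum 1.96 + 0.84 = 2.80 is the right multiplier when the standard error is effectively known, as it is with many independent units. Here the independent units that carry the treatment contrast are 12 schools. If the between-school variation is estimated from those schools, the arm effect has 12 − 2 = 10 degrees of freedom and the multiplier is larger. The design effect does not cover this. It inflates the variance for clustering, but does not allow for that variance being estimated from few clusters.

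At stake is the trial's only power statement for its primary outcome. If power at 7.9 min is 71–73% rather than 80%, the chance of missing a true difference of that size is 27–29% rather than 20%.

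**Working it through.** **Inputs** (all from 'Sample size' and 'Blinding and randomisation'): SD 18.6; ICC 0.01; 105 usable students per arm; 6 schools per arm, so 105/6 = 17.5 usable students per school; multipliers 1.96 (two-sided 5%) and 0.84 (80% power).

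**Step 1. Reproduce 7.9 min.** SE = SD × √(2 × DE / n), with DE = 1 + (m − 1) × ICC and n = 105.

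- m = 17.5: DE = 1 + 16.5 × 0.01 = 1.165; SE = 18.6 × √(2 × 1.165/105) = 2.771; detectable difference = 2.80 × 2.771 = 7.76 min.
- m = 25: DE = 1 + 24 × 0.01 = 1.24; SE = 2.859; detectable difference = 8.00 min.
- No clustering (DE = 1): SE = 2.567; detectable difference = 7.19 min.

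The stated 7.9 lies between the first two, where normal-theory power at 7.9 min is 81.4% and 78.9%. So the plan did use a design effect, and its figure is correct for the formula chosen. The SE implied by 7.9 is 7.9/2.80 = 2.821.

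**Step 2. Replace the normal reference with t on 10 df.** The two-sided 5% critical value is 2.228 and the 80% quantile is 0.879, so the multiplier is about 3.11. Power comes from the noncentral t distribution with noncentrality 7.9/SE.

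| SE used | Power at 7.9 min | Difference at 80% power |
|---|---|---|
| 2.771 (17.5 per school) | 72.9% | 8.62 min |
| 2.821 (implied by 7.9) | 71.4% | 8.77 min |
| 2.859 (25 per school) | 70.3% | 8.89 min |

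The first two rows give the headline range. The third applies the design effect for the recruited school size to the retained number of students, and is slightly worse.

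**Step 3. Check the type of model that is planned.** Simulation with 12 schools, 17.5 usable students each, SD 18.6, and a true difference of 7.9 min for power:

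| Test, ICC 0.01 | Type I error | Power |
|---|---|---|
| School-level t, 10 df | 5.0% | 73% |
| REML multilevel model, normal reference | 5.0% | 78% |
| ML multilevel model, normal reference | 5.9% | 82% |

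With an ICC of 0.03, which is my sensitivity value and not a figure in the document, the type I error of the REML model with a normal reference rises to about 6.4%. The school-level t test stays at 5%.

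**Step 4. What baseline adjustment could recover.** If adjusting for baseline MVPA scales the SE by √(1 − r²), then r = 0.4 gives 8.62 × √(1 − 0.16) = 8.62 × 0.917 = 7.90 min. The value 0.4 is an assumption; the document gives no baseline/post-test correlation.

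**The case against.** The strongest reply is that the planned analysis is a multilevel model and not a t test on 12 school means. At the stated ICC, a REML fit with a normal reference holds its 5% error rate and has about 78% power, within 2 points of the stated 80%. That stands. A reader might infer from the t(10) figures that the design simply lacks the claimed power; the document does not support so flat a reading, because it commits to no reference distribution, and that choice is commonly left to the analysis plan. But the near-agreement depends on the ICC being close to 0.01. Above that, the same test exceeds its nominal error rate.

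Three further stronger readings also fail.

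- **Arithmetic slip.** A reader might take 7.9 for a miscalculation. It is not; it follows from the inputs and multipliers shown.
- **Paired analysis.** A reader might cite 5 df because the schools are matched, which gives about 61–63% power and 9.7–9.9 min. The pairs are used for allocation, no paired analysis is stated, and those figures assume that matching brings no precision at all. They are a sensitivity case only, as is the ICC of 0.03.
- **Misread null result.** A reader might say that a null result will be over-interpreted. The document does not present 7.9 min as a target or a minimum important difference, nor does it say that a null result will be judged against it.

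It is also fair to say that covariate adjustment may offset the loss. MVPA is measured at baseline, but it is not among the adjusters given as examples, and the sample-size section counts no such gain. The offset is possible, not assured.

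**Conclusion.** The point holds at moderate weight. The 7.9 min figure is correct for a large-sample formula with a design effect, but that formula makes no allowance for having only 12 randomised schools. With 10 school-level degrees of freedom and the protocol's own SD, ICC and retention, power at 7.9 min is about 71–73%, some 7 to 9 points below 80%, and the 80%-power difference is about 8.6–8.8 min, or 0.7 to 0.9 min above the stated figure. A REML multilevel model with a normal reference comes close to the stated power only if the ICC is about 0.01.

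These results assume equal school sizes and no precision gain from matching or covariates. The conduct of the trial is not affected; what needs correcting is the stated sensitivity of the design.

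**What to change.** Recompute the sample-size paragraph with t quantiles on 10 df and 17.5 usable students per school. Then state either a detectable difference of about 8.6 min at 80% power, or about 73% power for 7.9 min.

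If the authors wish to count a gain from adjusting for baseline MVPA, they should name that adjustment and give the assumed baseline/post-test correlation with its source. About 0.4 would restore 7.9 min. If they prefer to keep the normal-reference figure, they should say that it relies on an ICC of about 0.01.

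The cost is one reworded paragraph and a slightly less favourable figure. No extra schools or students are needed.

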### Blinding and randomisation

In this cluster-RCT, recruitment and baseline data collection will be conducted prior to randomisation. Schools will be match-paired based on their size and SEIFA score and randomly allocated to either the intervention (6 schools) or wait-list control (6 schools) group by a computer-based random number generator. Randomisation will be conducted by an independent researcher not involved in the current study. Participants attending schools randomised to the intervention group will commence the program once baseline measures have been completed for all participants. Participants in the wait-list control group will be provided access to the intervention materials after the completion of the 6-month follow-up assessments.

### Intervention

RAW-PA is a 12-week multicomponent physical activity intervention that utilises a widely available and popular activity tracker to target physical activity levels, with supporting digital materials that have been designed to target evidence-based behaviour change strategies. The intervention has been informed by our pilot research (conducted August-December 2015; see ‘Development of RAW-PA’ below) that used participatory research principles involving adolescents in designing and reviewing the intervention structure and components. This approach has been used to ensure that the intervention is tailored to adolescents’ needs, which is important for instilling feelings of ownership and control [39]. The intervention consists of the following components: (a) wrist-worn Fitbit® Flex; (b) accompanying Fitbit® app (free to register and use); (c) interactive weekly individual and/or team ‘missions’ or ‘challenges’; (d) digital behaviour change resources including infographics, short informative and motivational videos and social forums, accessible via a private, proactively researcher-moderated Facebook page; and (e) alerts to new content and missions or challenges delivered via email and/ or text message ~2–3 times/week. The accompanying behaviour change resources match the theme of the weekly ‘mission’ and are designed to step participants through the behaviour change process in a flexible, interactive way. They are based on behaviour change techniques (described in more detail in the following sections) that are effective for changing behaviour at the individual and population levels [40]. The online delivery mode ensures that the digital resources are readily accessible for adolescents to engage with in their own time using computers or mobile devices. The intervention has been designed to target low-cost everyday physical activity (e.g. walking with friends, active transport) that can be integrated into adolescents’ daily lives. An overview of the weekly ‘missions’ is provided in Table 2.

### Theoretical basis of RAW-PA

Previous research has demonstrated that multicomponent [41], short-term technology-based interventions [33] can effectively increase adolescents’ physical activity levels. Interventions based on behavioural theories are also more likely to be effective than atheoretical approaches [42]. RAW-PA is grounded in Social Cognitive Theory [43] and Behavioural Choice Theory [44]. These theories recognise that health behaviours are influenced by factors operating at multiple levels including intrapersonal (e.g. enjoyment, self-efficacy) and interpersonal (e.g. families, teachers) influences. The core component of RAW-PA is the Fitbit® Flex, which incorporates 20 behaviour change techniques within the monitor and the accompanying app [23]. The additional RAW-PA interactive weekly ‘missions’ or ‘challenges’ and accompanying resources are designed to help students learn and develop key behaviour change techniques (e.g. self-monitoring, goal setting, social support, self-efficacy, action planning etc.) that are recognised as being critical for having the confidence to change and maintain changes in behaviour [40]. RAW-PA targets the accumulation of activity (steps) throughout the day and strategies for how to integrate more movement — typically walking — into daily life. Activity accumulation may be more appealing for inactive adolescents who may be disengaged from sport or higher intensity activities. An overview of the intervention approach, the targeted determinants, and the behaviour change techniques targeted by the weekly ‘missions’ is provided in Table 2.

**Table 2 Tab2:** Description of RAW-PA objectives, theoretical approach and behaviour change techniques targeted

Week	Theme	Intervention objective	Determinants or mediators^a^	Behaviour change techniques^b^[40]
1	Knowing is the First Step!	Familiarisation with the Fitbit® Flex	Knowledge	Self-monitoring behaviour
2	Build it Up!	Developing goal setting skills Identifying barriers to physical activity engagement	Self-efficacy Benefits/barriers	Goal-setting (behaviours) Problem solving
3	Pair Up!	Encourage friends/peers to increase their activity levels	Modelling behaviour Social support	Social support - practical Social support - emotional
4	The Happy Dance	Celebrating the achievement of set goals	Self-efficacy Benefits/barriers	Goal-setting (behaviours) Action planning Social reward
5	It’s a Social Movement	Providing social support for physical activity	Enjoyment Outcome expectations	Social support - practical Social support - emotional
6	Reach for the Stars!	Tracking activity levels across the day in comparison to sports stars	Enjoyment Self-monitoring and contracting	Problem solving Instruction on performing a behaviour Social comparison
7	Break it Up!	Identifying and sharing strategies for breaking up sitting time	Self-efficacy Modelling behavioural	Habit reversal Self-efficacy Social support - practical
8	Step it Up!	Evaluating and adjusting set goals	Self-efficacy Barriers/benefits	Focus on past success Review of outcome goals Set graded tasks
9	Buddy Up!	Support friends/family to increase their own physical activity	Modelling behaviour Enjoyment	Modelling behaviour Identification of self as role model
10	Mark it Up!	Identifying and sharing strategies for increasing steps at school Raising awareness of activity opportunities provided at school	Availability Access	Social support Social comparison Action planning
11	Globe Trotter	Evaluating set goals Reflecting on journey so far	Self-efficacy Outcome evaluations	Self-monitoring Review of outcome goals
12	Keep it Up!	Message reinforcement Confidence to be physically active	Knowledge Self-efficacy Benefits/barriers	Commitment Review of outcome and behavioural goals Relapse prevention

^a^Based on Social Cognitive Theory [43] and Behavioural Choice Theory [44]

^b^Behaviour change techniques from the Behaviour Change Technique taxonomy [40]

